### Loss to follow-up

We anticipate negligible loss of patients to follow-up. The Canadian Critical Care Trials Group (www.ccctg.ca), who endorsed this trial, has achieved virtually 100% follow-up to hospital discharge over all of its landmark RCTs [46-48]. Although we will be following survivors to ascertain 90-day mortality and relapse rates, we also expect close to 100% follow-up based on our previous CCCTG experience.

### Analysis of primary outcomes

The primary outcomes will be analyzed as follows:(i).*Rate of recruitment*: We will consider the main trial to be feasible if we achieve recruitment rates of at least 1 patient per month per participating site. We will report recruitment rates with 95% confidence intervals.(ii).*Adherence to treatment duration protocol*: We will consider the main trial to be feasible if 90% of antibiotic treatment courses are 7 ± 2 days in the shorter duration treatment arm, and at least 90% of antibiotic treatment courses are 14 ± 2 days in the longer duration treatment arm. We will report proportion of adherence with 95% confidence intervals.

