We have performed a systematic review of the existing literature [21], a national practice survey of Infectious Diseases (ID) and critical care physicians [28], a single center observational study [29], and a multicenter observational study [[name], [name], [name], [name], [name], [name], et al: Antibiotic Treatment Durations Among Canadian Critically Ill Patients with Bacteremia, forthcoming]. We have identified gaps in current evidence, documented extensive practice variation, and confirmed equipoise for a randomized controlled trial comparing shorter (7 days) versus longer (14 days) antibiotic treatment durations for bloodstream infections.

The primary aim of the Bacteremia Antibiotic Length Actually Needed for Clinical Effectiveness (BALANCE) main randomized controlled trial will be to determine whether 7 days (as compared to 14 days) of adequate antibiotic treatment is associated with non-inferior survival for critically ill patients with bacteremia. The aim of this BALANCE pilot randomized controlled trial is to determine whether recruitment and protocol adherence rates will be sufficient for the main trial to be feasible.

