### Setting

To maximize efficiency, the BALANCE pilot trial will aim to involve a geographically and clinically diverse spectrum of ICUs across Canada. The study will be initiated in October 2014 at Sunnybrook Health Sciences Centre (SHSC) in Toronto, Ontario, and then rolled out to additional sites, starting with Kingston General Hospital in Kingston, Ontario. These two sites will be sufficient to accrue the intended pilot sample size of 115 patients, but we aim to roll out to 13 additional sites, if sufficient funding is acquired, to improve external generalizability of the pilot trial findings. See Additional file 1 for participating pilot sites.

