### Statistical analysis

#### Sample size

To estimate our expected adherence rate of 90% within a margin of error of ± 5% (that is, actual adherence 85 to 95%), with 95% confidence, we plan to enroll 115 patients. At our expected recruitment rate of 1 patient/site month across 15 sites, we will need approximately 10 to 24 months to recruit these 115 patients given variability in site trial start-up steps (REB approval, data sharing agreements and contracts). By the time we have recruited 115 patients, we will know with 95% confidence that this number of sites would be able to recruit 95 to 138 patients over the same time interval in a future trial; this data will then be used to estimate the number of centers needed for the main trial (see Additional file 1 for detailed sample size calculation).

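### 115 patients do not give the stated ±5-point precision for adherence: it is about ±5.5 points pooled and ±7.8 per arm, before any allowance for differences between sites

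*Protocol article*

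**What the plan says.** The Sample size section gives the aim as "To estimate our expected adherence rate of 90% within a margin of error of ± 5" percentage points, spelled out as 85 to 95%, and continues "with 95% confidence, we plan to enroll 115 patients". It refers to Additional file 1, which is not shown, for the detailed calculation. The timeline assumes 15 sites ("At our expected recruitment rate of 1 patient/site month across 15 sites"). The Setting section says of the first two centres: "These two sites will be sufficient to accrue the intended pilot sample size of 115 patients". The 13 others depend on funding.

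Under Analysis of primary outcomes, the main trial is "feasible if 90% of antibiotic treatment courses are 7 ± 2 days in the shorter duration treatment arm". A separate clause sets the same 90% threshold for the other arm, with a window of two days either side of 14. On reporting, the section says "We will report proportion of adherence with 95% confidence intervals". No interval method is named. The threshold is applied arm by arm here, whereas the wording under Primary and secondary outcome measures can also be read as one pooled proportion.

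On who controls adherence, the treating team is told the stop date (Randomization and allocation concealment). A coordinator at each site visits daily (Trial interventions). The coordinator or site investigator prompts the team when it departs from the assigned date (Study drug related daily data).

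**The concern.** Adherence is one of the two feasibility criteria. The article makes a numerical claim about how well the pilot will measure it, so that claim can be checked.

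Two things look doubtful. First, 115 seems too few for ±5 points at 90%, even by the simplest formula, and that formula is applied to the pooled sample while the rule is applied to each arm. Second, the claim makes no allowance for site. Whether a course ends on time depends on a site's clinicians and on how actively its coordinator follows up, so patients at one site may resemble each other in adherence. The pilot is meant to show whether adherence will suffice for the main trial (Background), and Trial status plans further Canadian and international centres. For that use, variation between sites is part of the uncertainty.

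If the precision is overstated, readers will take the pilot's adherence figure as a firmer guide to the main trial than it is, above all if only a few sites open.

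**Working it through.** **Inputs from the article.** Expected adherence p = 0.90, margin d = 0.05, 95% confidence (z = 1.96) and N = 115 (Sample size). Sites: 15 (Sample size) or 2 (Setting). Rule applied per arm (Analysis of primary outcomes), so 57 or 58 patients per arm.

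**Assumed input.** The article gives no ICC for adherence. I use 0.02 and 0.05 as illustrations.

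**Step 1: the plan's own figure.** For independent patients, n = z² p(1 − p)/d² = 1.96² × 0.09/0.05² = 138.3, so 139. The stated 115 is not reproduced. Using 90% confidence gives 98. A Wilson interval at N = 115 has a half-width of about 5.5 points (83.2% to 94.3%). The same formula with d = 0.055 gives 114.3, so 115. Rounding 5.5 down to 5 is therefore a possible origin, but the article does not say so. The recruitment range in the same section does reproduce: exact Poisson limits for a count of 115 are 94.9 to 138.0, against the stated 95 to 138.

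**Step 2: precision that 115 delivers with no site variation.** Half-width = 1.96 × √(0.09/n).
- Pooled, n = 115: ±5.48 points (84.5% to 95.5%).
- Per arm, n = 58: ±7.72 points. With n = 57: ±7.79 points.

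**Step 3: is there room for site?** Any positive ICC multiplies the required n by a design effect above 1, so it would push the requirement above 139. A planned 115 therefore cannot contain such an allowance.

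**Step 4: size if sites differ.** Design effect DE = 1 + (m − 1) × ICC, where m is patients per site. Half-width = 1.96 × √(0.09 × DE/n). Sites are taken as equal in size and z is used throughout.

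| Sites | ICC | DE, pooled (m = 115/sites) | Pooled half-width | DE, one arm (m = 57.5/sites) | Per-arm half-width |
|---|---|---|---|---|---|
| any | 0 | 1.00 | ±5.5 | 1.00 | ±7.8 |
| 15 | 0.02 | 1.13 | ±5.8 | 1.06 | ±8.0 |
| 15 | 0.05 | 1.33 | ±6.3 | 1.14 | ±8.3 |
| 2 | 0.02 | 2.13 | ±8.0 | 1.56 | ±9.7 |
| 2 | 0.05 | 3.83 | ±10.7 | 2.39 | ±12.0 |

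With 15 sites, working per arm costs more precision than the assumed clustering does. With two sites, clustering could dominate the pooled margin.

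**Step 5: can a clustered interval be used with two sites?** A logit-scale interval with a t quantile on (sites − 1) degrees of freedom has 1 degree of freedom and t = 12.7. Take only the binomial variance at 90% of 115. The logit is 2.197 and its standard error is 1/√(115 × 0.09) = 0.311, so the limits are 2.197 ± 12.7 × 0.311, or about 15% to 99.8%. That interval is uninformative.

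**The case against.** A reader might infer that the interval to be reported is too narrow because it treats patients as independent. The document does not support that as a statement of fact. It names no interval method, and an article may leave the method to the analysis plan. One can say only that a plain binomial interval would be too narrow for inference to other sites if sites differ. For the participating sites taken as a fixed set, it would not be.

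A reader might also infer that a faulty interval drives the go/no-go decision. It does not: the rule compares an observed proportion with 90% and uses no confidence limit.

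Nor does the stated margin hold when all sites adhere alike. Step 2 shows that ±5 is missed even then.

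The ICC has no source in the document. The statement that earlier work "documented extensive practice variation" rests on a physician survey and observational studies. It does not show that sites differ in keeping to an assigned stop date under daily prompting. Weekly monitoring of adherence with the centres (Frequency of analyses) and recorded reasons for violations (Protocol violation) also make it less likely that a poorly adhering site goes unnoticed during the trial.

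These objections limit the clustering part to a conditional statement. They leave Steps 1 to 3 untouched. The unseen Additional file 1 cannot supply an allowance for site within 115, for the reason in Step 3.

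**Conclusion.** The concern holds in a limited form. The firm part is arithmetic on the article's own figures: 115 patients give about ±5.5 points pooled, not ±5, and about ±7.7 to 7.8 in each arm, where the analysis section applies the threshold. The pooled shortfall is about half a point. The per-arm margin is more than half as wide again as the stated one.

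It also follows that the stated precision contains no allowance for site, although adherence is managed at site level and the result is meant for further centres. How much this matters is not known. It rests on an assumed ICC, equal site sizes and a normal approximation. On those terms the effect is small with 15 sites (below one point at an ICC of 0.05) and large with two.

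None of this shows that 115 is too few for a feasibility pilot or that the go/no-go rule is wrong.

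**What to change.** Keep 115 patients and leave the go/no-go rule as it is.

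- **Sample size.** Restate the precision as at best about ±5.5 points for pooled adherence and about ±7.8 points per arm. Add that it is wider if sites differ and much wider if only a few open. Label any illustrative ICC as an assumption.
- **Analysis of primary outcomes.** Tabulate adherence by site and arm beside the 95% interval.
- **Supplementary analysis.** If enough sites open (for example about 15), add an interval with site as the cluster and a t quantile on (sites − 1) degrees of freedom. It will be somewhat wider than the z-based figures above, so those should not be presented as its expected width. With two sites, show the by-site figures only.

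This needs no extra patients, sites or data. The cost is a few sentences, one table and a less favourable stated margin.

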### Analysis of secondary outcomes

Mortality rates (at ICU discharge, hospital discharge and 90 days) will be measured as the proportion of patients alive or dead at these time points. We hypothesize that mortality rates will be non-inferior with 7 days of treatment; the main BALANCE trial will be powered to test this hypothesis. Continuous secondary outcomes, including lengths of stay in ICU and hospital, and durations of ventilation and vasopressor use, will be compared by Wilcoxon test. We will compare the ‘difference in differences’ between day 7 to 14 procalcitonin levels in the two treatment groups.

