#### Inclusion criteria

Patient is in the ICU at the time a blood culture result is reported as positive with a pathogenic bacterium.

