### Randomization and allocation concealment

Randomization will occur as soon as the consent is obtained. The web-based randomization system for BALANCE will be created using RANDOMIZE.NET (http://www.randomize.net/), and will employ variable block sizes, stratified by ICU site. After the full susceptibility results become available, the site research coordinator along with site co-investigators will determine the date for day 7 unblinding, taking into account the number of days that the patient has already received adequate antibiotics after the blood culture collection date. At day 7 (date entered by the research coordinator), another email will be sent with the unblinded treatment assignment for the patient. At this time the unblinded treatment for that patient will be displayed in the reports available to the site research coordinator. If a patient is randomized to the shorter (7 day) treatment arm, the treating team will be informed to stop the antibiotics at the completion of 7 days of antibiotics appropriate for the causative pathogen; if the patient is randomized to the longer (14 day) arm the team will be instructed to continue the antibiotic until that date.

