### Trial interventions

We will randomize patients to receive a shorter duration of adequate antimicrobial therapy (7 days) versus a longer duration (14 days). Adequate antimicrobial treatment will be defined as a regimen with *in vitro* activity against the organism(s) responsible for the bloodstream infection; the duration of adequate treatment will be determined as the cumulative number of calendar days for which adequate treatment is delivered beyond the date of collection of the index blood culture specimen- the clock will start from initiation of the first adequate treatment dose after the blood culture has been drawn. The selection of specific antimicrobial agents, doses and route of delivery will initially be at the discretion of the treating clinical team. Most commonly the patient will already be receiving some empiric antibiotic treatment for suspected infection prior to the blood culture being documented as positive; the study protocol will not expose patients to potential antibiotic treatment delays. As soon as blood culture results are available (preliminary Gram staining), the research coordinator, in consultation with the site investigator and site infectious diseases co-investigator if necessary, will review the initial antibiotic choice to ensure adequate empiric coverage for the potential culprit organism(s). As blood culture results are finalized (speciation and sensitivity determination), they will re-review the antibiotic choice to ensure that the spectrum of activity is adequate. If the spectrum is inadequate, this will be communicated to the treating physicians. To avoid differentially influencing antibiotic choices and clinical decision-making, the randomization assignment will not be communicated to the study research coordinator, study critical care or infectious diseases investigators or clinicians until the end of day 7. The ICU research coordinator at each site will visit daily to ensure protocol adherence (antibiotics are stopped at the pre-specified date (end of the 7th or 14th day) and not earlier (Figure 1).

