### Frequency and duration of follow-up

The antibiotic treatment durations may extend beyond ICU discharge for some patients, and beyond hospital discharge for a minority. Our retrospective observational study showed that 27% of patients were discharged from ICU to hospital wards on or before day 7 of adequate antibiotic treatment and 4% were discharged from hospital before day 7. Patients will be reviewed daily in ICU, at hospital discharge and at 90 days post-randomization. If a patient is discharged from hospital prior to 90 days post-randomization, the research coordinator will contact the patient (or substitute decision-maker as appropriate) by telephone to determine their disposition and vital status.

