### Primary and secondary outcome measures

The primary outcome for the main BALANCE trial is 90-day mortality and the primary outcome for the pilot trial is feasibility as defined by: (a) adherence to treatment duration protocol (proportion of treatment courses); and (b) rate of recruitment (patients per site, per month). We will consider the main trial to be feasible and worthy of embarking on a larger mortality-powered non-inferiority RCT if 90% of antibiotic treatment courses are within 7 ± 2 days in the shorter duration treatment arm or 14 ± 2 days in the longer duration treatment arm; and, if we achieve recruitment rates of at least 1 patient per 4 weeks, on average, per participating site. Secondary outcomes include ICU, hospital and 90-day mortality rates, relapse rates of bacteremia, antibiotic allergy and adverse events, rates of *Clostridium difficile* infection in hospital, rates of secondary infection or colonization with antimicrobial resistant organisms, ICU and hospital lengths of stay, mechanical ventilation duration, vasopressor duration in ICU and decline in procalcitonin levels.

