### Frequency of analyses

The BALANCE Pilot Trial will be conducted and reported according to recommendations by the Consolidated Standards of Reporting Trials (CONSORT), including analyzing patients in the groups to which they were originally assigned (intention-to-treat) and explicit procedures for handling of any missing data [49].

Analyses will be conducted at the completion of this pilot, given that there is no role for early termination [50]. However, we will monitor recruitment and adherence rates weekly, and examine barriers as needed, working with participating centers to provide screening and consenting tips from prior CIHR-funded ICU trials [34]. Capturing a minimal dataset of patient, pathogen and bacteremia source characteristics among eligible nonenrolled patients will facilitate this, and comparisons with eligible patients will help to identify selection bias [49].

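### The all-randomized comparison of ICU stay is valid but insensitive, because about a quarter of patients may leave the ICU before the arms differ; a day-7 landmark comparison should be added

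*Protocol article*

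**What the plan says.** All places are in the protocol article.

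- **Inclusion criteria.** Entry depends on ICU presence when the culture is reported: "Patient is in the ICU at the time a blood culture result is reported as positive with a pathogenic bacterium". Nothing requires the patient to be in the ICU at day 7.
- **Randomization and allocation concealment.** "Randomization will occur as soon as the consent is obtained". The Ethics and informed consent section allows consent up to the 7th day of adequate treatment. The coordinator enters a day-7 date, on which the assignment is released.
- **Trial interventions.** Concealment lasts through day 7 of adequate treatment: "the randomization assignment will not be communicated to the study research coordinator, study critical care or infectious diseases investigators or clinicians until the end of" that day.
- **Frequency and duration of follow-up.** In the sponsor's retrospective study, "27% of patients were discharged from ICU to hospital wards on or before day 7 of adequate antibiotic treatment". The figure for leaving hospital before day 7 is 4%.
- **Primary and secondary outcome measures.** The secondary outcomes include "ICU and hospital lengths of stay, mechanical ventilation duration, vasopressor duration in ICU and decline in procalcitonin levels".
- **Analysis of secondary outcomes.** Three time points are used for deaths: "Mortality rates (at ICU discharge, hospital discharge and 90 days) will be measured as the proportion of patients alive or dead at these time points". ICU stay, hospital stay, ventilation and vasopressor durations are compared by Wilcoxon test.
- **Frequency of analyses.** The analysis follows CONSORT, including "analyzing patients in the groups to which they were originally assigned (intention-to-treat"). No landmark at day 7 is mentioned.

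**The concern.** Until the assignment is released at the end of day 7, nobody who manages the patient knows the arm, so treatment cannot differ. A patient who has left the ICU for the ward by then has a first ICU stay whose length, ventilation days, vasopressor days and survival to ICU discharge were all settled beforehand. That patient can still do better or worse because of the assigned duration, but not on those measures of that stay. For everyone else, the whole-stay durations mix days when the arms are identical with days when they can differ.

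What is at stake is sensitivity. A real effect of treatment duration on later ICU stay will look smaller than it is among the patients who can show it, and a null result will be easy to over-read. The Trial status section says the pilot becomes an internal pilot, with its patients rolled into the main trial, if no substantive changes are needed. The way these outcomes are analysed now may therefore carry forward.

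**Working it through.** **Inputs from the article.** 27% out of the ICU on or before day 7 and 4% out of hospital before day 7, both from a retrospective cohort; 115 patients in total, so about 57 per arm. The 27% is an observed proportion and cannot be recomputed.

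**Inputs assumed.** The distribution of ICU stay after day 7, the size of any effect on it, ICU mortality among patients still in the ICU at day 7, and the share dying by day 7. The article gives none of these.

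**1. Patients affected.** 0.27 × 115 = 31, or 15 to 16 per arm. Remaining: 0.73 × 115 = 84, before subtracting early deaths. With an assumed 5% to 15% dying by day 7, the share still in the ICU is 0.73 − 0.05 = 0.68 down to 0.73 − 0.15 = 0.58.

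**2. ICU stay, Wilcoxon index.** Let θ be the probability that a patient in the longer-stay arm has the longer stay, among patients still in the ICU at day 7. Count stay from the start of adequate treatment, so that early leavers rank below all stayers. Pairs with at least one early leaver then average 0.5, and only pairs of two stayers carry a contrast:

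index in all patients = 0.5 + 0.73² × (θ − 0.5), with 0.73² = 0.533.

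With a lognormal post-day-7 stay (log mean 2, log SD 0.9; assumed) and a 1.5-fold effect, θ = 0.625. The index in all patients is 0.5 + 0.533 × 0.125 = 0.566. With early deaths also ranked low, the factor would be 0.68² = 0.46 down to 0.58² = 0.34.

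**3. ICU stay, power.** Simulated with 57 per arm, 27% leaving at a uniform time from day 1 to day 7, and a two-sided Mann-Whitney test at 0.05:

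| Post-day-7 stay (assumed) | Effect | All randomized | In the ICU at day 7 |
|---|---|---|---|
| Exponential, mean 8 days | 1.2-fold | 0.07 | 0.11 |
| Exponential, mean 8 days | 1.5-fold | 0.17 | 0.35 |
| Exponential, mean 8 days | 1.75-fold | 0.26 | 0.58 |
| Lognormal, as above | 1.5-fold | 0.23 | 0.51 |

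The landmark set has about 27% fewer patients and still has about twice the power at 1.5- to 1.75-fold. At 1.2-fold neither analysis has useful power.

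**4. ICU mortality.** Early live discharges add no ICU deaths, so each arm's proportion is multiplied by 0.73. With an assumed 30% against 20% among stayers:

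- Absolute difference: 0.73 × 30 = 21.9% against 0.73 × 20 = 14.6%, so 10.0 points becomes 7.3.
- Risk ratio: 21.9 / 14.6 = 1.50, the same as 30 / 20.
- Power at about 57 per arm: 17% in all patients, 18% restricted to stayers.

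This describes live discharges only. Deaths by day 7, equal in expectation in the two arms, would also pull the risk ratio toward 1, but that is true of any all-randomized mortality comparison, and the article gives no figure for them.

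**5. Ventilation and vasopressors.** Support already stopped by day 7 also carries no contrast, so the uninformative share is probably above 27%. The article gives no figure, and these durations were not simulated.

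**6. Hospital and 90-day mortality.** Early ICU leavers still receive their assigned duration, and only 4% had left hospital before day 7, so this mechanism hardly touches these outcomes.

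**The case against.** The strongest reply is that nothing here is an error. Analysing everyone as randomized validly estimates the effect of assignment, and a landmark comparison answers a different question about a narrower group. That stands, and it is why the landmark analysis should be added and should not replace the planned one.

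A reader might infer more: that dilution tilts the trial toward its non-inferiority hypothesis, or hides harm in patients who fail after stopping at day 7. The article does not support this. It leaves the non-inferiority test to the main trial, whose primary outcome is 90-day mortality, and states no margin or test for ICU mortality. The pilot's decision rests on recruitment and adherence alone, and the section on the data safety and monitoring committee calls the pilot underpowered for mortality. Late deaths after ICU discharge are caught by hospital and 90-day mortality, and relapse is a separate outcome. How ICU readmissions are scored is detail that a condensed article may leave to the full protocol or analysis plan, so its absence is no finding.

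Two further limits stand. The 27% comes from a retrospective cohort; consent may come as late as day 7, so the share among randomized patients is unknown. The power figures depend on assumed distributions and on fairly large assumed effects, in secondary outcomes with no powered test.

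**Conclusion.** The point holds as a minor one about sensitivity. Care is the same in both arms until the end of day 7, and the sponsor's own cohort suggests that about 27% of patients will have left the ICU by then. The planned all-randomized Wilcoxon comparison of ICU stay is valid but blunt: the departure of its index from 0.5 is multiplied by about 0.53, and power for a 1.5- to 1.75-fold effect is roughly halved under the distributions assumed above. For small effects the landmark gains little. Ventilation and vasopressor durations probably share the problem to an unknown degree. For ICU mortality the absolute difference shrinks by a factor of about 0.73, with the risk ratio and power essentially unchanged, so the only consequence is care in reading an absolute difference. Hospital mortality, 90-day mortality and the feasibility decision are not in question.

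**What to change.** Keep the intention-to-treat comparisons as planned. Add to Analysis of secondary outcomes a pre-specified landmark comparison, by the same Wilcoxon test, of ICU, ventilation and vasopressor days counted after the day-7 release date, among patients alive and in the ICU on that date. Membership of this set cannot depend on arm, because the assignment is still concealed when it is fixed, so the randomized comparison is preserved. Leave hospital and 90-day mortality in all randomized patients.

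The cost is a little more analysis work; the release date is already entered in the randomization system. The added comparison describes only patients still in the ICU at day 7, about 73% of the sample or fewer after early deaths, and should be labelled so. It is best settled before pilot patients are rolled into the main trial.

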### Subgroup analyses

To inform and possibly refine the main BALANCE Trial design, we will perform four exploratory subgroup analyses. The main subgroup analysis will be based on the underlying infectious syndrome causing bacteremia (vascular catheter-related, pneumonia, pyelonephritis, intra-abdominal, skin and soft tissue, other identified source, or unknown source). We will also perform subgroup analyses based on illness severity (APACHE II score of ≥25 versus <25), community- versus hospital-acquisition, and vasopressor use on day of randomization. If recruitment rates or protocol adherence are particularly low for any subgroups, in consultation with the Steering Committee and CCCTG, we will consider modifying definitions or procedures appropriately. For safety analyses, we will perform a per-protocol analysis by restricting the analysis to the participants who adhered perfectly to the protocol in terms of the eligibility, interventions, and outcome assessment.

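### Vasopressor duration is compared by an unadjusted Wilcoxon test although baseline vasopressor status is already recorded: a valid test, with a low-cost gain in precision available

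*Protocol article*

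**What the plan says.** In the protocol article, Analysis of secondary outcomes fixes one method for all the duration outcomes: "Continuous secondary outcomes, including lengths of stay in ICU and hospital, and durations of ventilation and vasopressor use, will be compared by Wilcoxon test". It names no covariate and no stratum.

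Subgroup analyses lists as subgroup factors "illness severity (APACHE II score of ≥25 versus <25), community- versus hospital-acquisition, and vasopressor use on day of randomization". Both APACHE II and vasopressor status must therefore be recorded at baseline. Their only stated analytic role is there: "we will perform four exploratory subgroup analyses".

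Randomization and allocation concealment says that the system "will employ variable block sizes, stratified by ICU site", so neither factor is balanced by design. The same section and Trial interventions withhold the assignment until day 7 of adequate treatment.

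The sample size, "with 95% confidence, we plan to enroll 115 patients", is set by the precision of the adherence estimate. No power, effect size or standard deviation is given for any duration outcome.

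**The concern.** A patient not on a vasopressor at randomization adds vasopressor days after that point only by starting one later. If late starts are uncommon, much of the spread in this outcome is already decided by a variable recorded at baseline. A two-group Wilcoxon test counts that spread as random error. It also carries any chance difference between arms in baseline vasopressor use straight into the observed comparison.

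The stake is the precision and readability of one secondary comparison in about 115 patients. An apparent difference in vasopressor duration could partly show which arm began with more patients in shock. Trial status adds a reason to settle the wording now: absent substantive protocol changes, pilot patients are to be carried into the main trial, so an analysis fixed here may be carried forward too.

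**Working it through.** The article gives no figure for vasopressor days, so there is none to reproduce. N = 115 and the design features come from the article. Every other input below is an assumption.

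**1. Chance imbalance.** With a fraction q on vasopressors at randomization and two roughly equal arms, the standard error of the between-arm difference is sqrt(4q(1−q)/115).
- q = 0.4: sqrt(0.96/115) = 0.091, so P(|difference| > 0.10) = P(|Z| > 1.09) = 0.27.
- q = 0.5: sqrt(1/115) = 0.093, so P = 0.28.
- Simulated trials with q from 0.3 to 0.7 gave 22 to 28%.

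**2. Share of rank variance explained by baseline vasopressor status.** Assumed: exponential durations rounded up to whole days, and late starters drawn from the same durations. Rank R² by baseline prevalence and by the share of non-users who start later:

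| On vasopressor at baseline | 5% start later | 15% | 30% |
|---|---|---|---|
| 30% | 0.81 | 0.59 | 0.37 |
| 50% | 0.77 | 0.61 | 0.41 |
| 70% | 0.59 | 0.48 | 0.33 |
| 85% | 0.36 | 0.29 | 0.21 |

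The range is 0.21 to 0.81. If the outcome also counts days before randomization, R² (with a severity score added) is 0.26 to 0.46.

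**3. What that means for precision.** An adjusted analysis has about (1 − R²) of the unadjusted variance, so 115 patients are worth 115/(1 − R²):
- R² = 0.2: 115/0.8 = 144
- R² = 0.5: 115/0.5 = 230
- R² = 0.7: 115/0.3 = 383

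For length of stay, under an assumed weak dependence on severity, R² was 0.03 to 0.04: 115/0.97 = 119 to 115/0.96 = 120.

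**4. Validity.** With no treatment effect, the unadjusted Wilcoxon test rejected in 4.9 to 5.5% of 3,000 simulated trials per setting. The adjusted rank test rejected in 4.4 to 5.3%.

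**5. Power if the effect acts from randomization.** With 15% late starters, mean duration 3 days and duration multiplied by exp(−0.8) = 0.45 in one arm, power without and with adjustment was:
- 30% on at baseline: 9% and 17%
- 50% on: 21% and 46%
- 70% on: 49% and 78%

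**6. Power if the effect acts only after the arms diverge.** With 40% on at baseline, mean 4 days, 15% late starters and duration ratio 2.0:
- effect from randomization: about 10 to 14% unadjusted and 35 to 41% stratified (van Elteren), across separate runs;
- effect only on days beyond 3, 4 or 5 days after randomization: 5% against 6%, 5% against 6%, and 5% against 5%;
- effect through later starts or restarts in all patients (15% rising to 30%): 17% against 26%;
- effect through later starts among non-users only (15% rising to 30%): 15% against 17%.

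The variance reduction in step 3 is present in every case. Whether it becomes useful power depends on when and how treatment duration acts on vasopressor use.

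**The case against.** The strongest reply is that nothing here is wrong. A rank test between randomized groups is valid, and its null distribution already allows for chance imbalance. An analysis plan that is not shown may add covariates. The outcomes are secondary in a pilot whose primary outcome is feasibility, and no power is claimed for them. The subgroup plan already takes an exploratory look by baseline vasopressor use. All of this stands, and it keeps the point at low severity. It does not remove the point: the article names a specific test, and a better one is available from a variable it already records.

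The second reply is that allocation is concealed until day 7 of adequate treatment and consent is sought as soon as cultures are positive. Many vasopressor days may therefore fall before the arms can differ. This also stands. Step 6 shows the power gain nearly vanishing when divergence comes 3 to 5 days after randomization. Consent may come as late as the seventh day of adequate treatment, so the gap will vary between patients, and the article does not give its distribution.

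A reader might infer more than the article supports:
- That most of the usable information is lost. This needs R² above 0.5, which holds in only part of the assumed range. The article does not say from when vasopressor duration is counted, and counting days before randomization keeps R² below 0.5.
- That the same loss applies to lengths of stay or ventilation. The length-of-stay gain is about 3 to 4%. Ventilation days were not examined, and the article does not show ventilation status at randomization as a recorded item.
- That mortality is fixed as an unadjusted analysis. The statement that it "will be measured as the proportion of patients alive or dead at these time points" defines the measure and rules out no adjustment.

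**Conclusion.** The point holds as a low-severity improvement in efficiency, confined to vasopressor duration. The planned test is valid. It leaves as noise a share of predictable variance that is likely to be material, about 0.2 to 0.8 of the rank variance under assumed baseline prevalence of 30 to 85% and late starts of 5 to 30%. It also does not correct a chance baseline imbalance, which exceeds 10 points in roughly one randomization in four. These sizes rest on assumptions, because the article gives no prevalence and no distribution of vasopressor days. The gain in power ranges from almost nothing to more than a doubling, according to when the arms begin to differ. No conclusion of the pilot about feasibility is affected.

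**What to change.** In Analysis of secondary outcomes, take vasopressor duration out of the common Wilcoxon sentence. State that it will be compared by a rank test stratified by, or adjusted for, vasopressor use on the day of randomization (van Elteren test or rank analysis of covariance), with the unadjusted Wilcoxon result reported alongside. APACHE II may be added as a continuous covariate for the other durations, but little gain should be expected there.

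The cost is a change of analysis wording. Both baseline variables are already needed for the planned subgroups, so no data item, visit or patient is added.
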